## **2.7 Sample size**

We anticipate that about 5% of participants in the standard of care group will present at the GP. This is a conservative assumption based on the experiences of similar campaigns in which individuals are approached in the community. With 2,400 adults randomized to each of the three study arms (total sample size of 7,200 adults), we will have >80% power (alpha=0.05, 2-sided) to detect a difference of at least 2 percentage points in attendance at GP practices.

However, since there is a possibility that a larger proportion of participants in the standard of care group will present at the GP, we have selected a sample size of 4,000 adults per arm (12,000 total) as this will ensure there is 80% power to detect a difference of at least 2 percentage points.

A small difference in the primary outcome would be meaningful given the low cost of the demand creation interventions. With 5 field workers distributing materials over a period of 10

weeks, ), the target of 12,000 adults reached by the field workers can be achieved by enrolling 48 individuals per day (which is feasible given the small amount of time needed to enrol an individual). HTS services at the GP practice will also start at the same time as the field work but will run for a period of 12 weeks. Provision of services at the GP practices will continue for an extra 2 weeks following the end of field work in order to allow individuals with the marketing material to still access HTS.

## **2.8 Process measures**

The study aims to rapidly measure whether demand creation framed according to behavioural economics principles will increase HIV testing and related services at GP practices.

**Process measures** will include:

### **1. Distribution of envelopes containing brochures of the different study groups in the community by the YCN field worker**

- Number of envelopes distributed in the community, by study group
- Demographics captured by the field worker of the target population that accepted the envelopes (age, gender)

### **2. Number of people attending the GP practice**

- Demographics captured by the GP practice of the target population that attends the GP practice for HTS services (age, gender), by study group
- The following category of individuals attending the GP practice will be monitored:
  - Individuals that have a brochure & self-reports that they were recruited by a YCN field worker
  - Individuals that do not have a brochure but self-reports that they were recruited a YCN field worker using demand creation material from a specific study arm
  - Individuals that have the brochure & self-reports that someone else (friend/family) gave it to them

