**Approach:** A randomized controlled trial to rapidly test two different low-cost demand creation interventions among adults residing in the catchment areas of GPCC programme clinics. For one group of participants, free HIV testing will be bundled with other health services that might be desired. Participants will receive a brochure that advertises the opportunity to receive free blood pressure testing and rapid glucose testing along with free HIV testing. This approach seeks to address stigma associated with HIV testing while also offering other health services that people value. For a second group of participants, the value of HIV testing will be emphasized using a 100 Rand voucher (US\$ 7) that can be redeemed for free services. This approach highlights the monetary value of the free services and seeks to leverage an endowment effect and loss aversion. A third group of participants will receive the standard of care promotion materials for HIV testing. The primary outcome will be presentation at the GP practice. Secondary outcomes will include HIV testing uptake, yield of new HIV-positive diagnoses, and yield of PLHIV who initiate ART. The study will be conducted at approximately five YCN GP practices in the Johannesburg Health District. We will seek to enrol 12, 000 adults in the vicinity of the GP practices who are willing to engage with a YCN field worker and willing to accept an envelope that contains one of the three HIV testing promotion strategies. The study duration will be approximately 10 months.

**Significance:** The standard marketing material (YCN brochure) and the YCN social media campaign have had limited success in increasing demand for HIV services offered by GP practices. There is a growing body of evidence from behavioural science showing that individuals' decision-making can be affected by the way in which information is presented and services are offered. We seek to test low-cost, easy-to-implement, demand creation strategies that can be implemented by the GPCC to increase demand for HIV services at GP practices.

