## **2.5 Recruitment procedures**

Each YCN field worker will use a recruitment script (Appendix 4) to engage with potentially eligible individuals and will then hand them a marked envelope. Individuals will be recruited individually or in groups. The handing out of brochures is a standard demand creation strategy and no informed consent will be obtained from individuals during this interaction. The field worker will only record basic demographics (age group, gender) on individuals who receive the study envelopes on the REDCap system. This will be completely anonymised and not linked to any personal identifying information and only used to determine aggregate statistics. YCN field workers will target areas in the GP's catchment area (or within a local taxi ride) specifically targeting high volume and high transit settings. Some recruitment sites will include the industrial zone/formal workspaces, informal workspaces (trading stalls, spaza's, salons, veggie stalls etc), retail/shopping zones, establishments that sell food, educational settings (TVET, university, trade schools, etc), commuter stops and other community settings (indoor and outdoor venues). We will be able to record which envelopes are distributed at the different recruitment sites on REDCap using the data fields on the distribution log (Appendix 5).

Individuals who are interested in the services provided by the GP and attend the GP practice will be asked about how they heard about the practice and requested to hand-in the brochure that they received. The individual will then be requested to sign a study consent form (Appendix 8 and

9) before any data is collected and sign an HTS consent form (Appendix 7) before any medical procedures. As part of the research study and routine procedures at the GP practice, we will ask participants some questions. Questions will include but are not limited to demographic information (age, gender, telephone number and primary home address) and HTS outcomes (Date of HIV test, HIV test result and ART start date).

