- **Study data set:** Study data will be constructed based on merged electronic data sets from REDCap and the ICS data extract using the ICS unique number.

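### Arm and recipient status for the primary outcome rest on the item a presenter brings or on self-report, and presenters are logged only after two consents, so attribution may differ by arm in a direction the protocol does not fix

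*Protocol*

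**What the plan says.** Section 2.6 defines the primary outcome for every adult who is enrolled and given information: did that person present at one of the practices? The route from envelope to outcome is spread over several sections.

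- **Hand-out.** Envelopes are marked and allocated to field workers in advance (2.4), and the distribution log can show which envelopes went to which recruitment site (2.5). The field worker records age group and gender, of which 2.5 says: "This will be completely anonymised and not linked to any personal identifying information and only used to determine aggregate statistics".
- **Material.** Brochures are stamped with the GP's name and telephone number (2.3). No study or envelope number on them is mentioned. The voucher is one "that can be redeemed for free services" (Study Summary). Section 2.3 says the lifestyle brochure and the voucher come in addition to the standard material, whereas 2.4 says each envelope holds one of three brochures.
- **Arrival.** Presenters are asked how they heard of the practice and to hand in the brochure (2.5). Section 2.8 monitors three groups. The first is holders recruited by a field worker. The second is "Individuals that do not have a brochure but self-reports that they were recruited a YCN field worker using demand creation material", whose arm is then known only by their own account. The third, covering pass-ons, is "Individuals that have the brochure & self-reports that someone else (friend/family) gave it to them".
- **Record.** Study consent is signed before any data are collected (2.5). The screening and enrolment log is completed after both the research and the HTS consent, and the ICS number is generated after both (2.9). The study data set is built from "merged electronic data sets from REDCap and the ICS data extract using the ICS unique number".

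**The concern.** The numerator of the primary outcome depends on three things that happen after randomisation: what the person brings, what the person recalls, and whether the person signs two forms. Each may be affected by the material received.

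- A voucher with a stated value may be kept, brought or passed on more readily than an information brochure.
- Someone drawn by the lifestyle screen may come for blood pressure and glucose and decline the HIV test. That person has presented in the sense of 2.6 but signs no HTS consent, so is not logged under 2.9.
- If intervention envelopes also hold the standard brochure, as 2.3 implies, an intervention recipient who brings only that item looks like a standard-of-care presenter.

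The first mechanism would tend to favour the voucher; the other two would work against an intervention arm. If attribution is unequal, the comparison is biased whichever way the imbalance runs, and a larger sample does not remove it. An analysis plan could settle which categories count, but it cannot recover a link that was never recorded.

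**Working it through.** **Inputs from section 2.7.** "We anticipate that about 5% of participants in the standard of care group will present at the GP". The test is specified as "alpha=0.05, 2-sided) to detect a difference of at least 2 percentage points in attendance at GP practices". The chosen size is 4,000 per arm. The protocol gives no attribution shares; those below are assumptions.

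**Step 1: the plan's own figure.** "With 2,400 adults randomized to each of the three study arms (total sample size of 7,200 adults), we will have >80% power". For 5% v 7% with n = 2,400, the pooled rate is 0.06.

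- se0 = √(2 × 0.06 × 0.94 / 2,400) = 0.00686
- se1 = √[(0.05 × 0.95 + 0.07 × 0.93) / 2,400] = 0.00685
- Power = Φ[(0.02 − 1.96 × 0.00686) / 0.00685] = Φ(0.96) = 83.1%

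The stated figure reproduces. With 4,000 per arm, power for 5% v 7% is 96.5%. The sample size is not at fault.

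**Step 2: model.** Recorded rate = true rate × share of presenters correctly attributed. With d the difference in recorded rates, the two-sided rejection probability is

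R = Φ[(d − 1.96 se0) / se1] + Φ[(−d − 1.96 se0) / se1].

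**Step 3: no true effect, 5% in both arms, n = 4,000.** Each arm truly has 0.05 × 4,000 = 200 presenters.

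| Attribution shares | Recorded presenters | Recorded rates | d (points) | R |
|---|---|---|---|---|
| 95% v 95% | 190 v 190 | 4.75% v 4.75% | 0 | 5% |
| 95% v 90% | 190 v 180 | 4.75% v 4.50% | 0.25 | 8.3% |
| 95% v 85% | 190 v 170 | 4.75% v 4.25% | 0.50 | 19.0% |
| 95% v 75% | 190 v 150 | 4.75% v 3.75% | 1.00 | 60.1% |

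For the third row, se0 = √(2 × 0.045 × 0.955 / 4,000) = 0.00464 and se1 is the same to that precision. The two terms are Φ(−0.88) = 0.189 and Φ(−3.04) = 0.001. R is the same whichever arm has the higher share.

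**Step 4: a true effect hidden.** Take a true 5% v 7% with attribution of 90% in standard of care and 80% in the intervention arm. The recorded rates are 4.5% v 5.6%, the difference shrinks from 2 to 1.1 points, and power falls from 96.5% to 61.3%. If instead 10% of the intervention arm's presenters are counted as standard of care, the recorded rates are 5.7% v 6.3% and power is 20.3%.

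**Step 5: equal loss.** If 20% of presenters are lost in both arms, type I error stays at 5% and power for 5% v 7% is 91.7%. Unequal loss is the problem, not loss as such.

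**Step 6: passages set side by side.** Section 2.6 counts anyone who presents; 2.9 logs only those who sign both forms. Section 2.6 also concerns adults who were enrolled, while 2.8 tells recipients from pass-on holders by self-report alone. Sections 2.3 and 2.4 disagree on what an envelope holds.

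**The case against.** The strongest reply is that the design has more of a link than this suggests, and much of it stands.

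- A reader might infer that nothing ties presenters to envelopes. The text does not support that. Envelopes are marked and logged by site, the brochure is requested on arrival, and a returned voucher or lifestyle brochure itself shows the arm. The forms in Appendices 5 and 6 may already carry an envelope number.
- A reader might also infer that non-presenters need an individual key. They do not: envelopes distributed by arm give the denominator, and an arm-only logistic regression needs only counts. Correct arm and recipient status among presenters is still required.
- The aggregate-use sentence in 2.5 describes the age-group and gender record; it does not forbid logging envelopes.
- The list in 2.8 is one of process measures. It does not say that recall assigns arm in the primary analysis or that pass-ons are counted, and an analysis plan may settle both.
- It is tempting to conclude that the errors favour the voucher. No passage says the voucher must be shown to obtain services, which are free at the point of care to everyone, and the hand-in request is the same in every arm. If the standard brochure is in every envelope, some errors run against the voucher.

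The reply leaves two things unanswered: the text describes no code that reaches the practice, and presenters are logged only after both consents.

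**Conclusion.** The concern holds in a limited form. As written, attribution of the primary outcome depends on the item brought, on self-report and on signing two consents, and the arms' materials give reason to expect unequal attribution. Unequal attribution is a well-founded risk, not a stated fact, and its direction is not known.

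The size rests wholly on assumed shares: false positives of about 8%, 19% and 60% for gaps of 5, 10 and 20 percentage points, at a 5% presentation rate with 4,000 per arm. The model treats unattributed presenters as lost; assigning some of them by recall would change the figures. Against a target of 2 points, a 10-point gap already shifts the recorded difference by 0.5 points, and the protocol as shown gives no means of measuring such a gap. Separately from any bias, 2.6 and 2.9 disagree on who counts as having presented. Both matters need settling before envelopes go out, because a missing code cannot be restored afterwards.

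**What to change.** 1. Put an identical card with a non-identifying serial code in all three envelopes, so that the reason to bring something is the same in each arm. Record the code in the distribution log and again at presentation, as a non-identifying count taken before and regardless of research or HTS consent, subject to ethics approval. If Appendices 5 and 6 already carry such a number, state it in 2.5 and 2.9.
2. Define the primary outcome as serials presented over serials distributed, by arm, each serial counted once. Report self-reported pass-ons separately and exclude them from the primary numerator.
3. Do not assign arm by recall. Report presenters without a code in a bounding analysis.
4. Reconcile 2.3 with 2.4 on envelope contents, and 2.6 with 2.9 on who counts as having presented.

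Individual matching on the logged age group and gender should not be used to verify recipients; it would conflict with the aggregate-only use in 2.5.

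**Cost:** one printed card per envelope, one field on two forms, and an ethics amendment, since 2.5 places consent before any data collection at the practice and the waiver in 3.1 covers only the field hand-out. Recorded rates will be slightly lower because uncoded presenters leave the numerator. Pass-on status will still rest on self-report, and the card makes the prompt to bring something equal without guaranteeing equal return.

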## 2.9 Data collection tools and data systems

Data will be collected and captured electronically by fieldworkers and HTS counsellors on the REDCap system. The data collection tools listed below will be built into the REDCap system. However, the study informed consent form and the HTS consent form will be completed on the paper-based form. All information relating to the participants' HIV and ART initiation status will only be captured on the Intelligent Care System (ICS). Below we provide a description of all the tools that will be captured both electronically and on paper.

- **Distribution log** (Appendix 5): This log will be used to track the distribution of envelopes in the community by the YCN field worker.
- **Participant consent for study participation** (Appendices 8 & 9): Individuals that present at the GP practice will be invited to participate in the study and interested participants will sign a written informed consent on a paper version.
- **Consent form for HTS procedures** (Appendix 7): As part of routine care, informed consent is obtained from all individuals before an HIV test is conducted. The HTS consent forms are the primary data collection source for recording HIV test results. Individuals interested in taking an HIV test will sign a paper version of the HTS consent form.
- **Screening and enrolment log** (Appendix 6): The screening and enrolment log will be completed on REDCap after the participant signs the research and HTS consent forms. In order to adhere to the Department of Health requirements for HIV testing, the identity numbers or date of birth of individuals who want to access HTS will be captured on REDCap. After the study consent form (Appendix 8 & 9) and the HTS informed consent (Appendix 7) are signed the individual's information will be captured onto the Intelligent Care System (ICS). The ICS system will then generate a unique identifier. Once the ICS-generated unique number is generated and the screening and enrolment log are captured electronically on REDCap, the individual's identity number or date of birth will be removed from the data set and the ICS unique number will serve as the participant study number.
- **Intelligent Care System (ICS)**: ICS is the existing GPCC patient record platform used to record demographics of all patients enrolled in the GPCC program including those tested

for HIV and those started on ART. HTS is captured onto ICS from the HTS consent forms and the GP's clinical files.

- **Study data set:** Study data will be constructed based on merged electronic data sets from REDCap and the ICS data extract using the ICS unique number.

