## **2.6 Study outcomes**

The primary outcome for this study will be presentation at the GP practice. For each adult who is enrolled in the study and given information about the GPCC, we will determine whether they presented at one of the GP practices.

Secondary outcomes will include the following:

- HIV testing uptake: We will assess whether participants complete HIV testing at GP practices. This outcome will be defined for all adults who are enrolled in the study.
- HIV-positivity among participants who get tested for HIV.
- Linkage to care among newly diagnosed individuals. We will assess whether participants who tested HIV-positive initiate ART at the GP practices.

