purposes of this research project will be extracted, delinked from any patient identifiers and will rely on the ICS system-generated patient number.

Data for monitoring and evaluation of the intervention will be de-identified at the point of data collection.

- The investigator team providing support for monitoring and evaluation of the demand creation strategies will not have access to any information that will identify the individual patients. Further, the investigators will not have access to any patient files. The ICS-generated patient number will serve as the unique study number in the data set.
- GP practices will be assigned a study practice number.
- Field workers and the GPs will collect data that will be used for monitoring and evaluation. This data will be documented on routine systems and study-specific forms that will not contain any information that can identify individual patients.
- After the study consent form is signed, individuals that attend the GP practice for HTS will be given a unique study identifier through ICS. Data collected for this study will be de-identified and cannot be fully anonymised because GPs need to verify whether individuals tested for HIV and were linked to care if tested HIV positive. The link between patient IDs and unique study numbers will be kept by the GP in a locked cabinet at the selected GP practices. In addition, the links will be kept separate from other study documents to reduce the chances of linking the unique study number to the patient's file number.
- In addition to the data being de-identified, we will also aggregate findings when reporting (i.e., no individual cases will be reported on).

The study databases resulting from data collection will not contain identifying information and will be organized by assigned study ID numbers. Databases will be stored on password-protected computers. All database files will also be password-protected, and only study staff will have access to the files. Hard copy documentation will be stored in locked cabinets (at the GP practice overseen by the implementing partner). On completion of the final dataset(s), hard copies of

study documentation will be scanned. The hard copies will then be destroyed, and the electronic copies of the originals will be kept for six years after study completion before destroying them.

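### Presentation, the primary outcome, is recorded only after both research and HIV-test consent, so presenters who do not sign both count as non-presenters, possibly more often in Group 1

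*Protocol*

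**What the plan says.** Section 2.6 defines the primary outcome for every enrolled adult given information about the programme: "we will determine whether they presented at one of the GP practices". HIV testing uptake is a separate secondary outcome.

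The data flow is set out elsewhere:

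- **Section 2.5.** An attender is asked how they heard of the practice and is asked to hand in the brochure. The study consent form is then signed "before any data is collected and sign an HTS consent form (Appendix 7) before any medical procedures".
- **Section 2.9, screening and enrolment log.** "The screening and enrolment log will be completed on REDCap after the participant signs the research and HTS consent forms". Entry on the Intelligent Care System (ICS), which generates the study number, also follows both signatures.
- **Section 2.9, HTS consent form.** "Individuals interested in taking an HIV test will sign a paper version of the HTS consent form".
- **Section 2.9, study data set.** REDCap and the ICS extract are merged on the ICS number.
- **Section 3.1.** Written consent from presenters is obtained so that the primary as well as the secondary outcomes can be reported. The same section foresees people coming for health services or for HIV testing.
- **Section 3.7.** Once the study consent is signed, "individuals that attend the GP practice for HTS will be given a unique study identifier through ICS".
- **Section 2.8.** Categories of attender are to be monitored (own brochure, no brochure but recruited, brochure passed on by someone else), but no tool is named for this.

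Section 2.3 offers weight, height, blood pressure and glucose checks in the Group 1 brochure only.

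**The concern.** The outcome as defined needs a yes or no for everyone given an envelope. The recording as described yields a yes only for presenters who agree to take part in research and sign the HIV-test form. Anyone else who walks in stays in the denominator and is indistinguishable from someone who never came.

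The two consents matter differently. Nothing suggests that willingness to join research depends on which envelope a person received, so that loss should shrink all arms roughly in proportion. The HIV-test form is another matter. Group 1's material is meant to attract people who are reluctant to test by offering other checks. If some of them come for those checks and do not sign the HIV-test form, Group 1 loses a larger share of its presenters than standard of care does. The primary comparison would then be biased against the bundled-screen strategy, on the very mechanism it is designed to exploit.

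**Working it through.** **Inputs from section 2.7.** The standard-of-care presentation rate is taken as about 5%. For the first sample size considered, 2,400 per arm, the section claims: "we will have >80% power (alpha=0.05, 2-sided) to detect a difference of at least 2 percentage points in attendance at GP practices". The selected size is 4,000 per arm.

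**Inputs assumed.** The share of presenters who do not sign both forms is not in the documents. Write it as s in standard of care and g in Group 1. The main table fixes s at 5% and varies g.

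**Formula.** For recorded rates a and b with n per arm, let m = (a + b)/2, then

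- SE0 = √[2m(1 − m)/n]
- SE1 = √[a(1 − a)/n + b(1 − b)/n]
- power = Φ[(|b − a| − 1.96·SE0)/SE1]

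**The plan's own figure.** With a = 0.05, b = 0.07 and n = 2,400: SE0 = 0.006856, SE1 = 0.006850, and (0.02 − 0.013437)/0.006850 = 0.958, so power is 83.1%. This agrees with the stated figure. At n = 4,000: SE0 = 0.005310, SE1 = 0.005306, and (0.02 − 0.010408)/0.005306 = 1.808, so power is 96.5%. The calculation is sound, but it assumes that every presenter is recorded.

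**Equal loss in both arms (n = 4,000, true 5% v 7%).**

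| Loss in each arm | Recorded rates | Power |
|---|---|---|
| 0% | 5.0% v 7.0% | 96.5% |
| 10% | 4.5% v 6.3% | 94.6% |
| 20% | 4.0% v 5.6% | 91.7% |

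Loss that does not depend on arm is a minor matter.

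**Unequal loss (n = 4,000, true 5% v 7%, s = 5%).** The recorded standard-of-care rate is 0.05 × 0.95 = 4.75%. The recorded Group 1 rate is 7% × (1 − g).

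| Group 1 loss g | Recorded Group 1 rate | Recorded difference (points) | Power |
|---|---|---|---|
| 5% | 6.65% | 1.90 | 95.6% |
| 10% | 6.30% | 1.55 | 85.9% |
| 12% | 6.16% | 1.41 | 79.3% |
| 15% | 5.95% | 1.20 | 66% |
| 25% | 5.25% | 0.50 | 18% |

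The recorded difference vanishes when 0.07 × (1 − g) = 0.0475, that is g = 1 − 0.0475/0.07 = 32%.

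**No true effect (5% in both arms, s = 5%).** The chance that Group 1 is declared significantly worse should be 2.5%.

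| Group 1 loss g | Recorded rates | Chance of appearing significantly worse |
|---|---|---|
| 10% | 4.75% v 4.50% | 7.7% |
| 20% | 4.75% v 4.00% | 37% |

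**The case against.** Only section 2.9 joins the two consents. Section 2.5 ties the HTS form to medical procedures rather than to data, and section 3.7 mentions only the study consent. Section 2.5 can be read as asking every attender to sign the HTS form before any procedure, including a blood pressure check, in which case Group 1 would lose few extra presenters. This stands as an ambiguity. It conflicts with the passage in section 2.9 that links the form to wanting an HIV test, and the two must be reconciled. It does not remove the problem, since on that reading someone who wants only the other screens must still sign an HIV-testing form or go unrecorded.

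Section 2.8 lists attender categories and section 2.5 collects brochures on arrival, so a separate count might be intended. But section 2.9 sets out to describe all the tools and includes no count before consent, and section 2.5 rules out collecting data before study consent.

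Three stronger readings are tempting and are not supported:

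- **That the loss does differ by arm.** This is an inference from the content of the brochures. It is reasonable for the HTS form and has no basis for research refusal.
- **That the primary outcome becomes the same as testing uptake.** Section 2.6 defines uptake as completing a test, and signing a form falls short of that.
- **That the trial is badly underpowered.** With 5% loss in standard of care, power stays near 86% at 10% loss in Group 1 and drops below 80% only at about 12%.

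**Conclusion.** The definition of the primary outcome and the way it is recorded do not match. Followed as written, the plan scores a presenter who does not sign both forms as a non-presenter. This rests on the text alone and needs no assumption. A later analysis plan could not repair it, because the missing arrivals would never have been recorded.

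The size of the harm does rest on assumptions. Loss common to all arms is nearly harmless. Bias against Group 1 is plausible through the HTS form and would matter at moderate gaps: against 5% loss in standard of care, 15% loss in Group 1 cuts the recorded effect from 2.0 to 1.2 points. The documents do not show where in this range the trial would fall. The sample-size calculation itself is not in error.

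**What to change.** Record presentation on arrival, before and independent of either consent, in an anonymous tally holding arm code, practice, date and the section 2.8 category (own brochure, no brochure but recruited, brochure passed on). State in section 2.6 that the primary outcome comes from this tally and how each category counts. State in sections 2.9 and 3.1 that consent gates only the HIV test, result and ART data. Reconcile sections 2.5 and 2.9 on who signs the HTS form and when.

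Print the envelope's arm code on every item inside it. Section 2.3 gives Groups 1 and 2 their item in addition to the standard material, so a Group 1 attender who hands in only an uncoded standard brochure would be tallied under standard of care.

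The cost is one short REDCap form, coded printing, and ethics approval to extend the section 3.1 waiver, which now covers only people approached in the field. The tally will still depend on self-report for recruits who arrive without a brochure, and the category field makes that visible.
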